## **I. Purpose, Background and Rationale**

### **A. Aim and Hypotheses**

**Although preventable, Cervical Cancer (CC) is the leading cause of cancer deaths among women in Sub-Saharan Africa with the highest incidence in East Africa.** In Kenya, CC contributes to over 80% of female reproductive-tract cancers, yet only 16.4% of eligible women are screened for cervical cancer and 31% become lost to follow-up during treatment. Innovative and feasible eHealth strategies have improved clinical outcomes and patient retention in low resource settings and could be key to improving CC screening and treatment coverage and retention in care in Kenya. **To address system level barriers to CC screening, treatment, and follow-up, our team worked with end-users (providers and patients) to develop and pilot the Cancer Tracking System (CATSystem),** an adaptation of a web-based eHealth intervention called the HIV Infant Tracking System (HITSytem). Using algorithm driven alerts for providers and SMS to patients, the CATSystem is designed to support CC screening, treatment, and referrals for reproductive age women (with/without HIV) in Kenya.

**Our overall objective in this proposal is to evaluate the efficacy, implementation, and cost-effectiveness of the CATSystem to improve CC screening, treatment, referral, and follow-up care in a matched, cluster randomized controlled trial in 10 Kenyan government hospitals (5 intervention, 5 standard of care [SOC]).** Specific aims (SA) include:

**Specific Aim 1:** Implement and evaluate the efficacy of the CATSystem to improve guideline adherent CC screening, treatment, referral, and follow-up.

*Hypothesis 1: Compared to standard of care, the CATSystem will result in higher rates of CC referral, treatment, and follow-up.*

*H2: Adjusted for pre-implementation CC screening rates, the CATSystem will result in higher screening rates compared to rates under SOC.*

**SA2:** Assess the feasibility and acceptability of CATSystem implementation in government hospitals.

*H1: CATSystem implementation in government hospitals will be deemed feasible and acceptable.*

**SA3:** Calculate costs and cost-effectiveness of the CATSystem to improve quality-adjusted life years gained.

*H1: The CATSystem will be a cost-effective intervention to increase QALY by increasing timely CC prevention and treatment to prevent more serious disease outcomes.*

### **B. Background and Significance**

**Cervical Cancer (CC) is preventable; yet in 2020, an estimated 604,000 cases were diagnosed and 342,000 deaths occurred globally. Over a third of these deaths occurred in Sub-Saharan Africa even**

**though only 14% of the world's female population live in the region.** In Kenya, CC accounts for 80% of female reproductive-tract cancers. Around 5,250 new cases of CC are diagnosed annually, and 3,286 women die of CC every year. Women living with HIV are particularly vulnerable to CC as HIV infection is associated with increased risk of human papillomavirus (HPV) infection and greater incidence and progression of cervical intraepithelial neoplasia (CIN). To achieve population level health gains, the WHO recommends countries reach 70% coverage with screening and treatment. Although awareness of CC screening amongst Kenyan women is high, uptake of screening and treatment remains low; only 10% of women 18-69 years of age have received effective CC screening. Low CC screening and treatment rates are largely due to resource constraints exacerbated by disjointed programs, and systemic health inequities driven by adverse social determinants of health (SDOH).

**In the ideal screen and treat protocol, treatment is administered during the same clinic visit as diagnosis for women with pre-cancerous lesions to minimize patient burden, treatment delay, and loss to follow-up (LTFU).** The main modality for immediate treatment (lesion elimination) is cryotherapy techniques, which mid-level providers can be trained to perform. Cases with more advanced cervical lesions are referred to provincial or referral-level hospitals for loop electrosurgical excision procedure (LEEP). Treatments for invasive CC (chemotherapy, radiation, radical hysterectomy) are referred to the highest tier referral hospitals – Moi Teaching and Referral Hospital (MTRH) in Eldoret (western Kenya) and Kenyatta National Hospital (KNH) located in the capital Nairobi. This is a barrier to treatment for many women given the geographic distance and expense.

### C. Rationale

**Web-based tracking systems and eHealth interventions have increased health access in low-resource settings and improve clinical outcomes, patient follow-up and adherence, and health communication.** Necessary eHealth infrastructure is widely available in Kenya (nearly 100% access to commercial wireless signal and 90% internet penetration) and can be leveraged to address many of the key barriers. Our intervention - **the Cancer Tracking System (CATSystem)** - harnesses the availability of wireless technology in Kenya to improve the provision of guideline adherent cervical cancer prevention and treatment. The CATSystem utilizes algorithm-driven alerts to increase coordination between key providers in various departments (Maternal and child health/Family Planning (MCH/FP), Comprehensive Care Center (CCC), laboratory) by serving as a single, linked medical record for a patient's CC care. It's technology also has the ability to extend the reach of expert providers into remote areas.

**CATSystem Intervention Overview.** Primary goals of the CATSystem are to: a) increase rates of CC screening/ rescreening to detect precancerous lesions or CC, and b) improve the same-day treatment, referral, and follow-up rates of women with positive screens. The CATSystem is web-based and accesses satellite broadband via modems. Its provider dashboard highlights patients with overdue services or those in need of outreach, and sends automated, customized texts to support screening and treatment follow-up per national guidelines. The CATSystem can securely store images of the cervix taken with colposcopes to allow for remote expert consultation if needed to correctly diagnose a patient or can be reviewed at clinical team meetings for input. This feature extends the reach of the limited number of CC experts in the country to optimize patient care and support provider capacity and confidence with CC diagnosis. The system was designed to mirror the ministry of health data collection forms, is compliant with Kenya's patient data protection laws, and can share data with Kenya's National Cancer Registry and Demographic & Health Surveys Program helping to strengthen existing national systems. It can also be interoperable with existing EMRs in Kenya. The CATSystem tracks and documents the following points of care:

1. Counseling,
2. Patient enrollment and information,
3. CC screening,
4. Treatment for pre-cancer,
5. Referral for treatment for invasive CC,
6. Patient tracking and follow up for women anywhere along the cascade.

## II. Research Plan and Design

## **A. Study Objectives:**

Our overall objective in this proposal is to evaluate the efficacy, implementation, and cost-effectiveness of the CATSystem to improve CC screening, treatment, referral, and follow-up care in a matched, cluster randomized controlled trial in 10 Kenyan government hospitals (5 intervention, 5 standard of care [SOC]). Specific aims (SA) include:

Specific Aim 1: Implement and evaluate the efficacy of the CATSystem to improve guideline adherent CC screening, treatment, referral, and follow-up.

*Hypothesis 1: Compared to standard of care, the CATSystem will result in higher rates of CC referral, treatment, and follow-up.*

*H2: Adjusted for pre-implementation CC screening rates, the CATSystem will result in higher screening rates compared to rates under SOC.*

SA2: Assess the feasibility and acceptability of CATSystem implementation in government hospitals.

*H1: CATSystem implementation in government hospitals will be deemed feasible and acceptable.*

SA3: Calculate costs and cost-effectiveness of the CATSystem to improve quality-adjusted life years gained.

*H1: The CATSystem will be a cost-effective intervention to increase QALY by increasing timely CC prevention and treatment to prevent more serious disease outcomes.*

## **B. Study Type and Design:**

We propose a cluster randomized controlled trial (SA1) enrolling CC screening clients at Kenyan health facilities: n=5 intervention and n=5 matched standard of care (SOC) sites to evaluate the efficacy of the CATSystem to improve guideline-adherent CC screening, treatment, referral and follow-up. SA2 will focus on the feasibility and acceptability of CATSystem implementation, and SA3 assesses the cost-effectiveness of the CATSystem and considerations for scale-up.

**Study Setting:** Kenya has a population of over 50 million people, of whom approximately 59.4% are reproductive age girls/women (15-64yrs). Proposed study sites will be in the Western Kenyan counties of Siaya and Busia where HIV prevalence is among the highest nationally, contributing to increased risk for cervical cancer. Siaya has a population of 993,183 (53% female) and the highest prevalence of HIV in Kenya (21%). Busia has an estimated population of 908,658, (52% female) and the 5th highest HIV prevalence in Kenya at 7.7%. The overall adult literacy rate is 81.5% in Kenya and 75.3% in Siaya and Busia. We have ensured our text messages have a 3 to 5 Flesch-Kincaid grade level. Table 1 details facility level data from the 10 most closely matched study sites from a recent retrospective review of 19 potential hospitals. Priority data points include the number of women: of reproductive age, living with HIV, screened for CC in the past year. We carefully reviewed and described the procedures and capacity for CC screening and treatment at each planned study site to ensure similarity across to optimize matching prior to randomization.

Table 1. Proposed matches from data reviewed October 2021 to September 2022

| Site                          | Busia | Bondo | Port Victoria | Akala | Matayos | Ukwala | Yala | Alupe | Nambale | Khunyangu |
|-------------------------------|-------|-------|---------------|-------|---------|--------|------|-------|---------|-----------|
| Repro aged women in care      | 51551 | 21368 | 8500          | 7060  | 5450    | 7196   | 6236 | 6000  | 5065    | 4156      |
| Women in HIV care (CCC)       | 3306  | 1200  | 591           | 2018  | 370     | 663    | 1271 | 249   | 700     | 1137      |
| Total screen/rescreen         | 4440  | 1878  | 1087          | 1003  | 359     | 477    | 617  | 478   | 730     | 615       |
| % repro-age women             | 8.6%  | 8.8%  | 12.8%         | 14.2% | 6.6%    | 6.6%   | 9.9% | 8.0%  | 14.4%   | 14.8%     |
| Trained providers (screening) | 10    | 10    | 8             | 6     | 7       | 6      | 3    | 5     | 4       | 3         |

Of 19 sites reviewed, this table shows the best 10 matched sites. All sites have VIA/VILI available for screening and will provide on site treatment with cryotherapy and/or thermocoagulation. Documentation of abnormal screening was variable due to inconsistent documentation. Based on data, we estimate an abnormal screen rate of 1%-5%.

**Study Design:** We propose a matched, cluster randomized controlled study design [2 arms, 5 intervention and 5 control hospitals (clusters), and at least n=30 patients with a positive CC screening result per cluster] to evaluate the efficacy of the CATSystem. The methods for Aims 1-3 are described below.

**Staffing and responsibilities.** We will hire and train one full time lay health worker as a Research Assistant (RA) per study site. Each site RA will be trained to conduct procedures specific to the study arm allocation and know the CC screening and treatment guidelines. Lay health workers have been effective and dependable RAs in prior HITSystem studies and programmatic work as they are already embedded in the facility/community and provide an opportunity to leverage existing relationships and build capacity through a train the trainer model. At all sites, RAs will assess eligibility and conduct informed consent procedures and surveys. At intervention sites, identified clinical staff will be trained on features of the system including how to routinely enter and update patient data, generate required county reports and follow-up with patients as appropriate. RAs will do the majority of data entry in the CATSystem at each participant visit, updating clinical information (services received, lab results, comorbidities, treatment, etc.) per clinician notes. RAs will also lead patient outreach and follow-up efforts (phone or SMS via CATSystem) and coordinate physical tracking, if needed, particularly for diagnoses that require timely treatment. Two Site Coordinators experienced in coordinating research activities on the ground will divide the responsibilities of overseeing activities at the 10 study sites.

## Procedures.

**Data Collection and Security:** At all study sites, patient-specific data including demographics; phone number and patient tracing information; patient health history; dates screened and treated; lab processing of PAP and biopsy tests, lab results, and follow-up screens will be entered directly into CATSystem by team members on password secured computers. The CATSystem was built in compliance with Kenya's 2019 Data Protection Act guidelines, is password protected, and maintains data for each client using numeric IDs to protect identities of participants and data exports in Excel. The system has been rigorously vetted by the KUMC Office of Information Security for vulnerabilities and passed both Security Headers and SSL labs test with a score of A and A+ respectively. At SOC sites, all clinical and CC screening service-related data will be collected in existing paper-based registries by health care providers per routine services. To prevent unintended intervention from health workers at control sites (reviewing clinical registers and entering participant data more comprehensively than they would in SOC setting), site coordinators will review paper registries at each control site visit and electronically enter patients' CC screening and treatment uptake data, using multiple sources (MCH, CCC, lab) to triangulate data. A parallel 'look-alike CATSystem' with all alerts, SMS, and patient tracking algorithms turned off, will be used for SOC data collection, to facilitate accurate, complete, and comparable data across arms. This process has been effectively used in our previous and current cRCT studies.

**Participant surveys:** A brief enrollment survey will collect patient-level data to better understand barriers experienced by patients, and assess CC knowledge, motivation to get screened, extent of partner support, mental health, risk of violence, language preferences, and education to gain a sense of literacy levels (both arms, Appendix 1). These instruments are modified from those used in HITSystem studies to assess changes that may mediate or moderate intervention impact. Women who screened positive for precancerous lesions during the study period will be asked to complete a survey including the same measures in addition to questions assessing their CC screening experience and treatment decisions within 6 months of the positive screen or at the conclusion of treatment (both arms, Appendix 2). Women diagnosed with invasive CC will be asked to engage in an interview to understand experiences accessing and receiving treatment at referral sites, the impact of the treatment process/disease on their psychological, social, physical, sexual, and financial health, and the type of support received and needed (both arms, Appendix 3). Costs associated with seeking screening and treatment will be included in these surveys. The remuneration plan for participant and provider surveys are outlined in the Human Subjects section.

**Facility assessment form:** will be completed at all sites at the beginning, mid-point and end of study implementation to assess resource level, annual CC screening volume, and CC screening provider-patient ratios to evaluate factors that contribute to implementation feasibility overtime. (See Appendix 4)

**Provider surveys:** At baseline and at the end of the study, providers in both arms will be asked to complete a survey (See Appendix 5). The survey will assess provider role/department, level of experience, knowledge and motivation regarding current CC screen and treat guidelines, and barriers and facilitators to provision of complete CC screening services. End of study surveys will also include level of direct engagement with CATSystem and adapted quantitative items from the Acceptability of Intervention Measure (AIM), Intervention Appropriateness Measure (IAM), and Feasibility of Intervention Measure (FIM) four-item measures of implementation outcomes that are often considered “leading indicators” of implementation success. Providers will be eligible to complete the survey if they (1) work primarily in CCC, laboratory, or MCH/FP departments, (2) will/have been involved in the provision of CC screening and treatment during the course of the study, and (3) have interacted with the CATSystem during the course of the study (intervention sites only). We estimate n=5 providers per site for a total of n=50 provider surveys (n=25 intervention, n=25 control). Providers will complete informed consent prior to surveys.

**Supportive Supervision Visits** will occur monthly at all sites. Site Coordinators will provide technical assistance and retraining, review study materials (informed consent forms, surveys), and review data for completeness and accuracy. The monthly frequency of site visits has been adequate in previous HITSystem studies.

Aim 2 methods will include surveys and focus groups with CATSystem users, described below:

**Surveys & focus groups with providers:** We will conduct semi-annual surveys (yrs 2 and 3) and FGD at each intervention site with all providers who routinely participate in CC screen and treatment services, including providers in the MCH/FP and CCC departments and laboratory staff (Appendix 6). We expect 5-8 providers with diverse levels of skill, years of experience and levels of knowledge involved in CC services at each site will participate in FGDs. The FGDs at intervention sites will be guided by TDF domains to understand *how* to best achieve the targeted CATSystem outcomes given the patient flow in their department and system-level challenges for the specific type of care they deliver. We will also monitor and elicit provider feedback on system and implementation modifications to better complement hospital workflow. *To ensure we are responsive to providers we will conduct FGD check in's twice a year in years 2 and 3 (see Appendix).*

**FGDs with women enrolled in CATSystem:** In year 3, two surveys and FGDs will be conducted at each intervention site: a) one with women enrolled in the CATSystem who received a positive screen and received appropriate treatment, and b) one with women enrolled in the CATSystem who received a positive screen and did not receive appropriate treatment. We expect 5-8 women in each of 2 FGDs per site (50-80 women total). Women who disengaged from CC care for >6 months but re-engaged after being prompted by Aim 2 engagement will still be counted as loss to follow-up for Aim 1 analyses. Similar to provider FGDs

we will use TDF domains to understand how participants experienced CC care, their experience with CATSystem, and factors that motivated them to complete treatment or describe barriers to treatment, see Appendix 7.

Procedures: Providers and participants who agree to participate will sign an informed consent specific to survey and FGD participation, respectively. FGDs will be conducted in a conference room at the facility, in the language the group feels most comfortable with (English, Kiswahili or both) and will be audio-recorded for later transcription and translation. FGDs will last approximately 30-45 minutes, allowing opportunity to learn from each other's experiences interacting with the CATSystem and identify opportunities to optimize the system.

Analyses for focus group discussions: FGDs will be digitally recorded and notes taken with participants' permission. Audio files will be translated and transcribed, coded, and analyzed using Dedoose, a qualitative data analysis software program. Transcriptions will be "open-coded": identifying key words and themes driven by the 14 specific TDF domains nested within the categories of Capability, Motivation, and Opportunity and provider recommendations for optimal implementation within existing health services. We will develop a codebook with typical exemplars for each theme, calculating the frequency and distribution of themes within larger topic areas. Two coders will establish inter-rater reliability and a third coder to settle discrepancies. Demographic and individual data will be summarized with descriptive statistics.

Aim 3 will use data collected in Aims 1 and 2 to calculate the cost-effectiveness of the CATSystem.

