### **C. Sample size, statistical methods, and power calculation**

**Outcomes. The primary outcome of SA 1** will be receipt of appropriate treatment (onsite or referral, as indicated) for clients with a positive screen. Figure 5 illustrates treatment scenarios for women with a positive screen and the targeted timeframe for treatment. Women with coinfections (cervicitis/STI) must receive treatment, resolution, and rescreening within 3 months to determine infection status and appropriate action. Patients with a positive screen for precancerous lesions should ideally receive same day onsite treatment with cryotherapy (max duration of 5 days/1 wk) or referral (in/outside facility) to LEEP for advanced lesions (w/in 5 days/1 wk) with treatment follow-up and negative rescreen. If suspected of invasive CC, a referral to KNH or MTRH for chemo/ radiotherapy within the month.

We will identify women presenting with precancerous lesions (mild, moderate or severe), suspicious of invasive CC, or those with unreliable screen results due to cervicitis/STI or other comorbidity in each arm. We will then determine if guideline adherent treatment was provided based on severity of screening results. Retention time from first screening to last follow-up will also be calculated and compared by arm. Patient and facility-level factors, including aggregated provider characteristics, will be assessed for their moderating impact on receipt of appropriate treatment after a positive screen. To assess pathways through which the CATSystem works, we will measure provider and patient information, knowledge and motivation as potential mediators pre- and post-intervention across arms.

Secondary Outcome: We will determine whether each participant is screened for CC during the intervention period and use these data to assess the effect of the CATSystem intervention on odds of screening. To adjust for sites' pre-intervention screening rates, we will compute the proportion of women screened for CC cancer during the pre-intervention period and include this variable as a covariate in modeling.

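### The 6-month safeguard on Aim 2 re-engagement leaves a gap in the CATSystem arm only: it can lengthen retention time, and can inflate treatment receipt if the treatment timeframes do not bind

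*Protocol*

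**What the plan says.** Section II.B, in the paragraph on focus groups with enrolled women, plans two surveys with focus groups at each intervention site in year 3. One is for women who were treated. The other is "one with women enrolled in the CATSystem who received a positive screen and did not receive appropriate treatment". Each group is expected to have 5–8 women, and no minimum interval since the positive screen is given. The safeguard follows: "Women who disengaged from CC care for >6 months but re-engaged after being prompted by Aim 2 engagement will still be counted" as lost to follow-up in Aim 1. SOC sites hold no such groups.

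Section II.C, repeated in V.B, says the primary outcome "will be receipt of appropriate treatment (onsite or referral, as indicated) for clients with a positive screen". Scoring depends on whether care followed the guidelines for the severity found. The timeframes are:

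- Precancerous lesions: the women "should ideally receive same day onsite treatment with cryotherapy (max duration of 5 days/1 wk"), with referral for advanced lesions on the same limit.
- Suspected invasive cancer: "a referral to KNH or MTRH for chemo/ radiotherapy within the month".
- Coinfection: the women "must receive treatment, resolution, and rescreening within 3 months".

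The text calls these timeframes targeted and refers to a figure that is not reproduced in the copy at hand. It adds: "Retention time from first screening to last follow-up will also be calculated and compared by arm".

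The missing-data paragraph of II.C plans two analyses. One counts dropouts as untreated; the other uses inverse probability of attrition weighting. Separately, the participant-survey paragraph of II.B surveys women with precancerous lesions in both arms, within six months of the positive screen or when treatment ends.

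**The concern.** The untreated focus group is filled with women who, at that moment, are failures on the primary outcome. Inviting them to the hospital to talk about untreated lesions may bring some of them back into care. The protocol recognises this, since it writes a rule for it. But the rule starts at six months of disengagement, while the outcome timeframes are one week, one month and three months. A woman can therefore be untreated, and so eligible for the group, well before the rule covers her. The protocol does not say how she is scored if she is then treated.

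The contact is a research activity, is not part of the CATSystem, and happens in one arm. Any treatment or visit that it prompts and that is credited counts for the CATSystem. If invitation dates are not recorded, the effect cannot be separated out afterwards.

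**Working it through.** **1. Are recently screened women available to invite?** Enrolment runs 24 months (II.C), and the trial occupies years 2 and 3 (V.A, Aim 3 analyses). Year-3 groups therefore run while women are still screening positive.

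**2. The plan's own power figure.** Inputs from II.C, sample size considerations: 0.10 vs 0.35, five clusters of 30 per arm, ICC 0.05, one-sided alpha 0.025.

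- Design effect = 1 + 29 × 0.05 = 2.45.
- Variance = (0.10 × 0.90 + 0.35 × 0.65) × 2.45 / 150 = 0.3175 × 2.45 / 150 = 0.00519; standard error 0.0720.
- Noncentrality = 0.25 / 0.0720 = 3.47, with 8 degrees of freedom.
- Power from the noncentral t = 85.87%, against a stated 85.9%. It is reproduced.

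The plan's separate simulated figure of 86.9% was not re-run.

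**3. Size of the pool.**

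- Untreated group: 5 sites × 5–8 = 25–40 women.
- Expected untreated in the CATSystem arm: 150 × 0.65 = 97.5.
- Share: 25 / 97.5 = 26% to 40 / 97.5 = 41%.
- One credited conversion adds 1 / 150 = 0.67 points.

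**4. Effect if the timeframes do not bind.** The documents give neither the share invited at six months or less nor the share then treated. I assume 25–50% for each.

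The first range has some support. With uniform accrual, proportional invitation and a group held between enrolment months 12 and 24, the share screened in the previous six months is 6/24 = 25% to 6/12 = 50%. The second range is assumption only.

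| | Low | High |
|---|---|---|
| Conversions | 25 × 0.25 × 0.25 = 1.6 | 40 × 0.50 × 0.50 = 10 |
| Points added (÷ 150) | 1.0 | 6.7 |
| CATSystem rate, planned 0.35 | 0.360 | 0.417 |
| Odds ratio vs 0.10, planned 4.85 | 5.07 | 6.43 |
| CATSystem rate if no true effect (0.10) | 0.110 | 0.167 |
| Rejection with no true effect, formula in step 2 | 3.6% | 16.0% |
| Rejection with no true effect, simulated | 3.6% | 18.7% |

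The simulation drew beta-binomial clusters with ICC 0.05, used a cluster-level t test and ran 20,000 trials. Without conversions it rejects in 2.49% under no effect and 85.6% under the planned effect.

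**5. Effect if the timeframes bind.** A woman first treated after her timeframe stays a failure, so late first treatment adds 0 points.

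**6. Retention time.** It runs to the last follow-up and has no window. A visit prompted by an invitation at six months or less can extend it under either reading.

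**7. The safeguard where it does apply.** It labels women lost to follow-up, not untreated. The first missing-data analysis treats these as the same. The second could weight known failures out as attrition.

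**The case against.** **The outcome may already be closed.** The group is defined by failure to receive appropriate treatment, which is the primary outcome itself. The text sets a maximum duration for lesions, uses mandatory wording for coinfection, and scores adherence to guidelines. The exact cut-off may also be left to a statistical analysis plan that is not at hand. This stands in part. A reader might infer that the primary outcome is inflated; the documents support only that it can be. The wording is mixed (targeted, ideally), and the negative rescreen after treatment has no deadline, so the point is open.

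**The 6-month rule need not imply that late treatment counts.** Loss-to-follow-up status also matters for retention time and for the attrition analyses. This stands: the rule's existence does not show that late treatment is credited.

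**SOC women are contacted too.** The six-month survey of women with precancerous lesions, and the interview of women with invasive cancer, take place in both arms. That may reduce the number still untreated. But contact common to both arms does not balance an additional contact in one.

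**A return may be a true effect.** Intervention-site follow-up includes phone, SMS and physical tracing (II.B, staffing). A woman a few months out may return because of these, so not every treatment after an invitation is bias. This stands, and it is a reason against simply discarding everything after the invitation.

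**The size is modest.** This stands. Ten conversions is the top of the assumed range, not its centre. A reader could also take the ceiling, with every attender invited early and later treated, which lifts 0.35 to 0.517–0.617. Nothing in the documents suggests that.

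**Conclusion.** The point holds as a gap in the safeguard, not as a demonstrated bias. The rule covers only women disengaged for more than six months. Untreated CATSystem women can be invited at any time after a positive screen, and SOC sites have no equivalent Aim 2 contact.

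Retention time is exposed on either reading. Treatment receipt is exposed only if the timeframes in II.C do not bind. In that case the likely size is 1.0–6.7 points, against a planned difference of 25 points, and rejection with no true effect is about 3.6–19%. Both ranges rest on the assumed 25–50% shares. If the timeframes bind, the figure for late first treatment is zero.

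The power statement needs no change. The correction is cheap and is worth making before the first year-3 invitation.

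**What to change.** 1. In the focus-group paragraph of II.B, invite women to the untreated group only after their Aim 1 outcome window has closed, and no earlier than the disengagement point of more than six months that the existing rule uses. The rule then covers every invited woman.
2. Score treatment receipt at a fixed time from the positive screen, identical in both arms, and reconcile II.B with II.C and V.B. Which clinical window applies is for the sponsor to decide.
3. Log the date of each Aim 2 invitation, and do not count contacts prompted by it toward retention time.
4. State that these women count as untreated in both missing-data analyses and are not weighted out as attrition.

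Freezing each invited woman's status at her invitation would look simpler. It would, however, cut follow-up short in the CATSystem arm only and so create a new imbalance.

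The cost is a few sentences, one date field, and a somewhat smaller and less recent pool for the untreated focus group. Clinical follow-up of the women is unaffected.
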